##### 2.6.1.3. Moderation analyses

To investigate whether treatment effect is moderated by baseline characteristics (baseline CAPS-5, PCL-5, DES, BDI-II, AAQ-II scores, and CPTSD diagnosis), Condition × Time × Moderator interaction effects will be tested with the primary outcome measures (CAPS-5, ITQ, and PCL-5) as dependent variables.

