There is not enough evidence to have *a priori* expectations with regards to the differential effectiveness of standard EMDR therapy compared to EMDR 2.0 or the Flash technique. Based on the results of earlier research on EMDR 2.0 and the Flash technique [e.g., (39, 48)], we expect that all interventions will be effective in terms of a significant reduction of (complex) PTSD symptoms and loss of diagnostic status. We also expect that all interventions will be effective in reducing the symptoms associated with PTSD. Considering the moderators, we expect that participants who show higher baseline symptoms of depression, will experience more difficulties in retrieving positive memories based on studies suggesting a negative memory bias in individuals with depression (51, 52). Therefore, we expect them to benefit less from the Flash technique than from EMDR therapy or EMDR 2.0. Furthermore, we expect participants who show relatively higher levels of experiential avoidance (defined as attempts to avoid thoughts, feelings, memories, physical sensations, and other internal experiences) and symptoms of dissociation at baseline, will benefit more from the Flash technique than from EMDR therapy. The reasoning underlying this hypothesis is that during the Flash technique only brief exposure to traumatic material is needed (42). Therefore, participants who are more avoidant, or tend to dissociate, will likely have less difficulty performing the Flash technique, than EMDR therapy. Based on the results of Matthijssen et al. (39), EMDR 2.0 is expected to be more efficient than standard EMDR therapy in treating traumatic memories and PTSD symptoms. Based on the preliminary findings of Brouwers et al. (48), we expect that the Flash technique will be rated as more acceptable by patients than standard EMDR therapy.

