#### 2.3.3. Assessments

At baseline assessment (T0), the CAPS-5 will be administered by a trained therapist, along with the Life Events Checklist for DSM-5 (LEC-5). The International Trauma Questionnaire (ITQ), PTSD Checklist for DSM-5 (PCL-5), Dissociative Experiences Scale (DES), Beck Depression Inventory-II (BDI-II), Brief Symptom Inventory (BSI), and the Acceptance and Action Questionnaire-II (AAQ-II) will be administered digitally. The baseline assessment takes approximately 90 min. After the baseline assessment and the session where the treatment plan is drawn up, a 6-week treatment phase commences during which participants fill out questionnaires weekly prior to the treatment sessions (T1-6). Questionnaires include the PCL-5, BDI-II, BSI, and AAQ-II and take approximately 30 min in total to complete. After the first treatment session (T2), a questionnaire about treatment acceptability is administered. After the treatment phase, a 12-week phase commences where no actual treatment is delivered, but participants fill out the PCL-5, BDI-II, BSI, and AAQ-II bi-weekly (T7-12). The treatment acceptability questionnaire is administered again at T7. The CAPS-5, ITQ, and DES are administered 4 weeks after treatment is completed (T8), and 12 weeks after termination of treatment (T12). To minimize missing data, reminders will be sent out to the participants to fill out the questionnaires. For a complete overview of the timing of the interventions and assessments, see Figure 1.

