#### 2.6.1. Aim 1: Treatment effectiveness

##### 2.6.1.1. Outcome measures CAPS-5, ITQ, and DES

To investigate the effectiveness of the three treatment conditions, the average scores will be estimated for the outcome variables at each time point for the three conditions. The baseline values will be included as covariate in the model. This will result in 3 (Condition: EMDR, EMDR 2.0, and Flash) × 2 (Time: T8 and T12) average score estimates. To investigate the differential effectiveness in reducing PTSD, complex PTSD and symptoms of dissociation of the treatments, these average score estimates will be compared across the three conditions. To answer the research question if the treatment arms are effective in reducing PTSD, complex PTSD, and symptoms of dissociation over time, the average scores of measurement occasions T0 vs. T8 and T0 vs. T12 will be compared using *t*-tests.

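### For CAPS-5 and ITQ, the named moderation test (Condition × Time × Moderator) shows only whether moderation changes between T8 and T12, so moderation of equal size at both visits is invisible to it

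*Protocol article*

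**What the plan says.** Section 2.6.1.3 gives its purpose as "To investigate whether treatment effect is moderated by baseline characteristics". The single test it names is: "Condition × Time × Moderator interaction effects will be tested with the primary outcome measures (CAPS-5, ITQ, and PCL-5) as dependent variables". It does not restate the time points or the role of baseline, and it names no Condition × Moderator test.

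The model for CAPS-5 and ITQ is in section 2.6.1.1. There, "The baseline values will be included as covariate in the model", and the result is "3 (Condition: EMDR, EMDR 2.0, and Flash) × 2 (Time: T8 and T12) average score estimates". For the arm comparison, "these average score estimates will be compared across the three conditions". Section 2.3.3 places T8 at 4 weeks and T12 at 12 weeks after treatment, so neither visit falls before or during treatment.

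The hypotheses are in section 1.4. Of patients with more depressive symptoms at baseline it says "we expect them to benefit less from the Flash technique than from EMDR therapy or EMDR 2.0". Patients with more experiential avoidance or dissociation are expected to gain more from Flash than from EMDR.

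**The concern.** The plan defines the treatment effect differently for its two groups of outcomes. For the frequently repeated questionnaires (section 2.6.1.2) it is the Time × Condition interaction, so adding a moderator gives a three-way term. For CAPS-5 and ITQ (section 2.6.1.1) it is a difference between condition means at T8 and at T12, so moderation of that effect is Condition × Moderator. Section 2.6.1.3 applies the three-way form to both groups.

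For CAPS-5 and ITQ the named test therefore asks whether moderation drifts over an eight-week follow-up interval (12 − 4 weeks). A patient characteristic that stably predicts who does better on which treatment would usually be reported as no moderation. A significant result would show a change in moderation over follow-up and could be misread as moderation of benefit. CAPS-5 is the outcome with blinded assessors (section 2.3.2), and the Discussion intends the moderator results to help match patients to treatments.

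**Working it through.** **1. What the three-way term is.** Write the section 2.6.1.1 model, with moderator m added, for visit t (T8 or T12) and condition c:

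E[Y_t] = α_t + β·Y_0 + γ_t·m + δ_ct + θ_ct·m

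Here θ_ct is the Condition × Moderator effect at visit t, relative to the reference arm. With two time levels:

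- Condition × Time × Moderator = θ_c,T12 − θ_c,T8
- If θ_c,T8 = θ_c,T12 = θ, the term is θ − θ = 0 for every θ.

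With complete data on both visits, testing this term is the same as testing Condition × Moderator on the difference Y_T12 − Y_T8, from which a stable θ has cancelled. This needs no numerical assumption and does not depend on sample size.

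**2. The plan's own sample size.** Section 2.5 gives no figure for moderation. Its arm size is used below, so it was checked first.

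- d = 0.65/√(1 − 0.25) = 0.751; two-sided alpha = 0.05/3 = 0.0167
- Non-centrality at n = 39: 0.751 × √(39/2) = 3.31 on 76 df, giving power 0.804 (n = 38 gives 0.792)
- 3 × 39 = 117; 117/0.9 = 130

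This reproduces the plan's 39, 117 and 130.

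**3. Size of the loss, by simulation.**

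- From the plan: three arms of 39; baseline explains a quarter of the variance (coefficient 0.5, since 0.5² = 0.25; residual SD √0.75).
- Assumed, because the document gives no values: standardised moderator independent of baseline; moderation in one arm only; slope in outcome SD per moderator SD; residual T8–T12 correlation 0.4, 0.6 or 0.8; alpha 0.05; complete data.
- 2,000 runs per setting; omnibus F test on 2 df. Monte Carlo standard error near 5% is √(0.05 × 0.95/2000) = 0.5 percentage points.

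Rejection rates with moderation equal at T8 and T12 (correlation 0.4 / 0.6 / 0.8):

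| Slope | Condition × Time × Moderator (named test) | Condition × Moderator on T8/T12 mean, baseline-adjusted |
|---|---|---|
| 0.40 | 5.9 / 5.0 / 4.7% | 67 / 61 / 55% |
| 0.65 | 5.1 / 4.8 / 4.4% | 97 / 95 / 94% |
| 0.90 | 5.4 / 5.2 / 4.4% | above 99% throughout |

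Rejection rates with unequal moderation (correlation 0.6):

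| Slope at T8 → T12 | Named test | Condition × Moderator on the mean |
|---|---|---|
| 0.65 → 0.30 | 49% | 77% |
| 0.65 → 0 | 95% | 44% |

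The named test responds to the change between visits and to nothing else.

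**4. If T0 were an outcome level.** The contrast of T0 with the T8/T12 mean detects equal moderation of slope 0.65 in 85–91% of runs over the same correlations. A three-way term would then be meaningful, but section 2.6.1.1 does not specify that model.

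**The case against.** **The premise is carried over from another section.** Section 2.6.1.3 does not say that T0 is a covariate or that Time has two levels, and section 2.6.1.1 also compares T0 with T8 and T12 by t-tests. If T0 were an outcome level, the three-way term would be an ordinary moderation test. This is a fair caution. However, those t-tests address change over time, apart from the arm comparison. The only model shown for CAPS-5 and ITQ has baseline as covariate and two post-treatment levels, and the moderation section does not bring T0 back.

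**The wording might mean moderator slopes compared across arms within each visit.** That would answer the hypothesis, but it is a Condition × Moderator comparison and the text names a different interaction. A fitted three-way model does contain the lower-order term. Since the plan does not name it as the test, relying on it after a null three-way result would be a post hoc choice.

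**Low power for moderators is already conceded.** The Discussion concedes this for small effects only. Here a large stable effect is missed as well, at any sample size.

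**A reader might infer that the test misses all moderation present at both visits.** It does not: moderation fading from 0.65 to 0.30 is present at both and is picked up in 49% of runs. Only equal moderation gives a term of exactly zero.

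**A reader might also infer that a main aim of the trial is lost.** The abstract does call moderators the second aim. Section 1.4 places them within the first aim, the analysis sits under the Aim 1 heading, and section 2.4.2 lists moderators among secondary parameters. The PCL-5, also a primary outcome, is scored weekly from before the first session, so its three-way term can pick up courses that diverge during treatment.

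**Conclusion.** The point holds for CAPS-5 and ITQ. Under the only model the article gives for them, the named test measures the T8-to-T12 change in moderation and does not test the section 1.4 hypotheses of differing overall benefit. For moderation of equal size at both visits, rejection at the alpha level is an algebraic result that rests only on section 2.6.1.1 governing the moderation analysis. The power forgone (about 55–67% at slope 0.40, 94–97% at slope 0.65) depends on the assumed slope, correlation and alpha and illustrates scale only.

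This should be fixed. It is not a fatal flaw: it concerns a moderator analysis for two of three primary instruments and leaves the main arm comparison and the sample size as they are.

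**What to change.** In section 2.6.1.3, for CAPS-5 and ITQ, name Condition × Moderator in the baseline-adjusted model as the moderation test, and state whether it is evaluated at T8, at T12 or averaged over both. Keep Condition × Time × Moderator only as a separate question: does moderation change over follow-up? The PCL-5 wording can stay.

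Alternatively, state that T0 is kept as an outcome level for this analysis and test the T0-to-T8 and T0-to-T12 contrasts. The first option is simpler. It keeps the model of section 2.6.1.1, and baseline CAPS-5, itself a listed moderator, does not also become an outcome value.

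The cost is a few sentences, settled before outcome data are analysed. No new data, visits or participants are needed.

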#### 2.6.2. Aim 2: Treatment efficiency

A survival analysis will be performed to investigate the efficiency of the interventions on symptom level. Estimates will be used to determine how much time is needed to reach a clinically significant change and a cut-off score on the PCL-5. Clinically significant change will be calculated by means of a Reliable Change Index (85). A cut-off score of 33 on the PCL-5 will be used, based on Bovin et al. (63) and Wortmann et al. (86). The estimates for the three treatment conditions will be compared using a log-rank test. A survival analysis is preferred since it accounts for censoring, which happens when not all participants reach a clinically significant change or the cut-off score during the course of the trial. Time will be defined by the amount of treatment sessions and ranges from one to six.

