## 2. Methods and analysis

### 2.1. Participants

Participants will be recruited at the Altrecht Academic Anxiety Center in Utrecht, Netherlands. The Altrecht Academic Anxiety Center is an academic outpatient mental healthcare clinic, specialized in diagnosing and treating obsessive-compulsive disorders, anxiety disorders, and trauma-related disorders. The study participants will be patients diagnosed with PTSD who have applied for treatment. The inclusion criteria are as follows: a primary diagnosis of PTSD, a minimum age of 18 years old, an estimated IQ of > 80, and sufficient understanding of the Dutch language. The use of benzodiazepines, alcohol, and other drugs is contraindicated for treatment and will be tapered as much as possible before participation. Exclusion criteria are: acute suicidality [as assessed by a senior clinician, and using the suicidality module of the mini-international neuropsychiatric interview; MINI; (53)], following concurrent treatment for PTSD, and any changes in psychopharmacological medication during the study or 6 weeks prior to participation, with the exception of tapering benzodiazepines.

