### 2.3. Procedure

#### 2.3.1. Recruitment and screening

The study will be conducted at the Altrecht Academic Anxiety Center. Individuals with PTSD symptoms will be approached by their therapists to participate in the current study. If written consent has been given, the research assistant may contact individuals directly as well. Those who are interested in participating will be invited for an appointment with one of the research assistants. During this appointment, the study will be explained and patients who wish to participate are asked to sign an informed consent-form. After consent, the Life Events Checklist for the DSM-5 (LEC-5) will be administered, along with a screening questionnaire assessing age, completed education, previously followed trauma-focused treatment, medication use, alcohol- and drug use, and suicidality. If patients report suicidal thoughts, suicidality risk will be assessed using the suicidality module of the MINI. If patients report a high risk of suicidality on the MINI., a senior therapist trained in the assessment of suicidality will make a final decision about the participation. By administering the Clinician-Administered PTSD Scale for DSM-5 (CAPS-5) and the screening questionnaire containing questions about the in- and exclusion criteria, it will be determined whether patients meet the criteria for participation.

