##### 2.4.1.1. Clinician-Administered PTSD Scale for DSM-5 (CAPS-5)

The Dutch version of the CAPS-5 (58, 59) is a clinician rated structured interview to assess PTSD diagnosis and symptom severity over the past month. The severity of each symptom is scored on a 0–4 scale. A sum score is computed and can range from 0 to 80. The CAPS-5 is considered to be the golden standard for assessing PTSD and shows high internal consistency and modest interrater reliability (60).

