##### 2.4.1.2. PTSD Checklist for DSM-5 (PCL-5)

The Dutch version of the PCL-5 (61, 62) will be used to measure PTSD symptom severity over the past week. The PCL-5 is a 20-item self-report measure with total scores ranging from 0 to 80, and is widely used in scientific papers, which improves the comparability of the results. The monthly version of the PCL-5 has good internal consistency, test-retest reliability, and convergent and discriminant validity (63). The weekly version of the PCL-5 is currently still undergoing psychometric evaluation (64).

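### The PCL-5 cut-off event in the efficiency analysis has no starting-score condition, so patients already below 33 before treatment count as successes at the first time point

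*Protocol article*

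**What the plan says.** **Entry.** Section 2.1 of the protocol article states: "The inclusion criteria are as follows: a primary diagnosis of PTSD, a minimum age of 18 years old, an estimated IQ of > 80". Section 2.3.1 explains how eligibility is established: "By administering the Clinician-Administered PTSD Scale for DSM-5 (CAPS-5) and the screening questionnaire containing questions about the in- and exclusion criteria". The PCL-5 plays no part in it.

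**The two instruments.** The CAPS-5 is a "clinician rated structured interview to assess PTSD diagnosis and symptom severity over the past month" (2.4.1.1). The PCL-5 is a self-report scale from 0 to 80 that "will be used to measure PTSD symptom severity over the past week" (2.4.1.2).

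**The efficiency events.** Section 2.6.2 states: "Estimates will be used to determine how much time is needed to reach a clinically significant change and a cut-off score on the PCL-5". The cut-off is 33, and the arms are compared with a log-rank test. Where the section explains censoring, it joins reliable change and the cut-off with *or*. On the clock it says: "Time will be defined by the amount of treatment sessions and ranges from one to six".

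**Timing and analysis set.** The PCL-5 is given at T0. Then, according to 2.3.3, "participants fill out questionnaires weekly prior to the treatment sessions (T1-6"). The same section places T2 after the first session. Section 2.6 sets intention to treat for the analyses in general and names no exclusion for the survival analysis.

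**The concern.** The time-to-event analysis is meant to show how many sessions a patient needs to get below a threshold. That has meaning only for patients who start on the other side of it. The plan screens on a clinician's rating of the past month and then counts success on self-report of the past week. An eligible patient can therefore score 28 on the PCL-5 at T0. If that score stays below 33, the patient meets the event at the earliest possible time with no improvement. A patient who goes from 24 to 31 has worsened and still counts.

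The abstract describes efficiency as time to lose the PTSD diagnosis and time to reliable change. The cut-off appears to stand in for the first of these, yet the patient with 28 meets it while holding the diagnosis that qualified him or her for the trial.

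Section 1.4 predicts that EMDR 2.0 is more efficient than standard EMDR, and section 3 draws consequences for waiting lists and costs. Patients who needed no sessions to be below 33 make every arm look faster and add events that carry no information about treatment.

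**Working it through.** **1. The plan's own figure.** Section 2.5 gives a sample size for a pairwise t-test and none for the survival analysis. Inputs: d = 0.65, a quarter of the variance explained by baseline, two-sided alpha 0.05/3, power 0.80.
- Effective size: 0.65/√(1 − 0.25) = 0.751.
- The two-sample t-test needs 38.6, so 39 per arm; 3 × 39 = 117; 117/0.90 = 130.

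The stated 39, 117 and 130 reproduce, and this point does not touch them.

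**2. Share already below 33.** The documents give no baseline PCL-5 mean or SD. Assuming a normal score with mean m and SD s, the share is Φ((33 − m)/s).
- m = 55, s = 10: Φ(−2.20) = 1.4%
- m = 50, s = 12: Φ(−1.42) = 7.8%
- m = 48, s = 12: Φ(−1.25) = 10.6%
- m = 45, s = 12: Φ(−1.00) = 15.9%
- m = 45, s = 15: Φ(−0.80) = 21.2%
- m = 42, s = 14: Φ(−0.64) = 26%

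The range is about 1 to 26%. A share of 10 to 20% is 13 to 26 of 130 patients.

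**3. Effect on apparent early success.** Let f be the share already below 33 and h the true chance of an event per session. If all of them are counted at session one, the session-one share is f + (1 − f)h. With h = 0.10 (assumed):
- f = 0: 10%
- f = 0.05: 0.05 + 0.95 × 0.10 = 14.5%
- f = 0.10: 0.10 + 0.90 × 0.10 = 19%
- f = 0.20: 0.20 + 0.80 × 0.10 = 28%

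**4. Effect on the log-rank test.** Simulated pairwise test: sessions 1 to 6, 43 per arm (130/3), 4,000 runs per setting. Per-session event chances are assumed. Power when these patients are counted as session-one events, against leaving them out:

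| Event chance per session, alpha | Nobody below 33 | 10% below: counted / left out | 20% below: counted / left out |
|---|---|---|---|
| 10% v 20%, 0.0167 | 61.1% | 48.6% / 55.8% | 38.9% / 49.6% |
| 10% v 25%, 0.0167 | 90.3% | 82.4% / 87.9% | 69.6% / 81.1% |
| 10% v 22%, 0.05 | 87% | 79% / 84% | 69% / 80% |

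The differences are 7.2, 5.5 and 5 points at 10%, and 10.7, 11.5 and 11 points at 20%: roughly 5 to 11.

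With equal arms (10% v 10%, alpha 0.0167), the rejection rate is 1.6 to 1.8% whether these patients are counted or left out.

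The simulation makes every such patient an event at session one. One whose score rises to 33 or more at the first assessment would not be, so the dilution shown is towards the upper end for a given share.

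**The case against.** **The point rests on silence.** The plan speaks of reaching a cut-off and the abstract of losing a diagnosis. Both suggest a passage from above to below, and a fuller document could restrict who is at risk. This stands in part: nowhere does the article say in words that patients already below 33 are events. But 2.6.2 already fixes instrument, threshold, test and time axis, and 2.6 sets intention to treat. Followed as published, the rule counts them.

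**It may be one joint event.** The first sentence joins change and cut-off with *and*, which could mean that both are required. The later *or*, and the two quantities named in the abstract, favour separate events. If a joint event was meant, the section still needs correcting.

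**T1.** A reader might infer that a T1 score below 33 must be booked as one session. The documents do not support that. T1 comes before session one, so it is zero sessions and lies outside the stated range. The natural reading is that T2 to T7 are sessions one to six. What remains is a mapping that is not stated.

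**Bias.** A reader might also infer that the comparison is biased or gives false positives. It is not: randomisation spreads these patients over the arms in expectation, and the test already allows for chance imbalance.

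**Reach.** Nor does the whole efficiency hypothesis hang on this event. Reliable change is tested as well, and section 3 adds the intervention time needed to lower disturbance scores.

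**Size.** The full fall in power, for example from 61% to 39%, should not be charged to the rule. Part of it comes from having fewer informative patients, which no rewording recovers.

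**Conclusion.** The concern holds for the cut-off event only. Entry has no PCL-5 threshold, the event is an absolute score with no starting condition, and the published rule therefore counts untreated, unchanged patients as the fastest responders. The result is overstated early success in every arm and a weaker log-rank contrast, not type I error inflation or systematic bias.

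If 10 to 20% start below 33, the cost is roughly 5 to 11 points of power relative to leaving them out, and the session-one event share in an arm with a true 10% rises to 19 to 28%. Both figures depend on an assumed baseline distribution and assumed event rates. If baseline severity is high, with only about 1% below 33, the effect is negligible. The primary comparisons and the sample size are untouched. The correction is worth making because it needs only data already being collected.

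**What to change.** In section 2.6.2:
- Restrict the cut-off survival analysis to participants with a T0 PCL-5 of 33 or higher. T0 precedes randomisation (2.3.2), so the subset is defined at baseline and the randomised comparison is kept. T1 would be a poorer basis, since by then allocation is known in an open trial.
- Keep all randomised participants in the reliable-change analysis.
- State that T1 is zero sessions and that T2 to T7 correspond to one to six sessions.

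The cost is a change of wording and somewhat fewer patients in the cut-off analysis: about 13 to 26 fewer of 130 under the 10 to 20% assumption. No new data are needed. Requiring reliable change in addition to the cut-off is optional; the starting-score condition alone cures the defect.

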### 2.5. Sample size

To perform a power analysis for a multilevel model, it is required to estimate parameters based on earlier research (83), which was not possible for the interventions investigated in the current study. Power analyses were performed in G*Power 3.1.9.2, based on three pairwise comparisons between the conditions (EMDR therapy vs. EMDR 2.0, EMDR therapy vs. Flash, EMDR 2.0 vs. Flash) on the post-treatment measurement occasion. The power analysis is based on a two-sided *t*-test, in which two independent means will be compared with a Bonferroni-corrected alpha for the three pairwise comparisons = 0.0167 (0.05/3), power = 0.80 and Allocation ratio = 1. We aim to be able to detect a clinical meaningful difference between the conditions, what comes down to a medium to large effect size *d* = 0.65. To increase the power, we will include the baseline CAPS-5 score as a covariate in the analyses (84). By doing so, we expect to explain approximately a quarter of the variance at the post-treatment measurement. The residual variance reduces and gives us a sample size of *n* = 39 per condition, or *N* = 117 in total. To account for an expected 10% dropout, we will recruit a total 130 participants.

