##### 2.6.1.2. Outcome measures PCL-5, BDI-II, BSI, and AAQ-II

For the outcome measures administered (bi)-weekly, a multilevel model will be performed. The baseline values will be included as covariate in the model. It will be investigated if the treatment conditions are effective in reducing self-reported PTSD symptoms (PCL-5), comorbid symptoms (BDI-II and BSI) and experiential avoidance (AAQ-II) over time. To investigate the differential effectiveness of the treatments, a Time × Condition interaction will be tested with the outcome measures as dependent variables. To investigate the effectiveness of the treatments, the effect of time will be tested with the outcome measures as dependent variables.

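### The efficiency comparison on time to a PCL-5 of 33 uses a log-rank test that ignores baseline PCL-5; adjusting for it would recover power at almost no cost

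*Protocol article*

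**What the plan says.** Section 2.6.2 of the protocol article sets up a survival analysis with two PCL-5 events: "Estimates will be used to determine how much time is needed to reach a clinically significant change and a cut-off score on the PCL-5". For the second event, "A cut-off score of 33 on the PCL-5 will be used". The time axis is short and discrete: "Time will be defined by the amount of treatment sessions and ranges from one to six". On the test itself the article says "The estimates for the three treatment conditions will be compared using a log-rank test". It names no covariate or stratification factor.

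PCL-5 is among the questionnaires given at T0 (section 2.3.3): "The International Trauma Questionnaire (ITQ), PTSD Checklist for DSM-5 (PCL-5), Dissociative Experiences Scale (DES), Beck Depression Inventory-II (BDI-II), Brief Symptom Inventory (BSI". For the PCL-5 scores over time, section 2.6.1.2 says "The baseline values will be included as covariate in the model". Section 2.5 adds baseline CAPS-5 to the post-treatment comparison in order to gain power: "By doing so, we expect to explain approximately a quarter of the variance at the post-treatment measurement".

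Section 1.4 gives aim 2 a directional hypothesis: "EMDR 2.0 is expected to be more efficient than standard EMDR therapy in treating traumatic memories and PTSD symptoms". Section 2.3.2 stratifies randomization by complex PTSD only, and section 2.1 states no PCL-5 threshold for entry.

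**The concern.** A fixed target score is easier to reach for a patient who starts near it. With a target of 33 and at most six sessions, someone starting at 38 and someone starting at 60 face different tasks whatever the treatment. A log-rank test without a baseline term leaves this known difference between patients in the noise.

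Two things follow. The comparison has less power than the same data could give. And because starting PCL-5 is not balanced by design, an arm that happens to start closer to 33 will tend to look more efficient. Efficiency is one of three stated aims, and the Discussion links a positive result to treating more patients and to shorter waiting lists.

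**Working it through.** **The plan's own figure.** Section 2.5 gives alpha = 0.05/3 = 0.0167 two-sided, d = 0.65, and a quarter of the variance explained by baseline. The adjusted effect is 0.65/√(1 − 0.25) = 0.65/0.866 = 0.751. A two-sample t-test then needs 39 per arm (power 80.4%), or 117 in total, and 117/0.9 = 130. The stated 39, 117 and 130 reproduce. At 39 per arm without the covariate, power would be 66.4%. So the plan already relies on a baseline covariate for its CAPS-5 comparison. It states no power for aim 2.

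**Inputs for the efficiency check.**
- From the article: cut-off 33, six sessions, 130/3 ≈ 43 per arm, d = 0.65, 10% dropout, and √0.25 = 0.5 as the baseline-to-post correlation. The last is stated for CAPS-5 and is carried over here to PCL-5.
- Assumed, because the article does not give them: baseline PCL-5 mean 45 to 55, SD 12, a drop of about 14 points over six sessions under EMDR, and reliable-change thresholds of 10, 15 or 18 points.

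**Tests compared.** Over event times t, the plain log-rank test is Z = U/√V, with U = Σ(d₁ₜ − dₜn₁ₜ/nₜ) and V = Σ dₜ(n₁ₜ/nₜ)(1 − n₁ₜ/nₜ)(nₜ − dₜ)/(nₜ − 1). The adjusted version regresses each patient's log-rank contribution on T0 PCL-5 within arm, subtracts the fitted part from U, and reduces V accordingly.

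**Simulation A** (EMDR 2.0 versus EMDR, everyone at or above 33 at T0, d = 0.65 at session 6, 4,000 runs per setting, two-sided 5%), cut-off event:

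| Baseline mean | Between-patient variance 72 of 144 | Between-patient variance 100 of 144 |
|---|---|---|
| 45 | 35.7% → 43.9% (+8.2) | 48.5% → 60.3% (+11.8) |
| 50 | 50.6% → 60.8% (+10.2) | 55.7% → 67.7% (+12.0) |
| 55 | 56.8% → 66.7% (+9.9) | 60.1% → 71.7% (+11.6) |

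Reliable change: 51.5% → 56.6% (10-point threshold) and 71.7% → 75.6% (18-point threshold).

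**Simulation B** (different trajectories, 10% dropout, baseline mean 50, 6,000 runs per setting, two-sided 5%):

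| Event and setting (six-week drop, EMDR vs EMDR 2.0) | Plain | Adjusted log-rank | Stratified by T0 tertile |
|---|---|---|---|
| Cut-off, all ≥ 33, r = 0.5, 14 vs 26 | 55.8% | 68.4% (+12.6) | 63.8% (+8.0) |
| Cut-off, no floor, r = 0.5, 14 vs 26 | 50.6% | 65.4% (+14.8) | 59.0% (+8.4) |
| Cut-off, no floor, r = 0.5, 14 vs 22 | 26.3% | 35.2% (+8.9) | 30.4% (+4.1) |
| Cut-off, no floor, r = 0.43, 14 vs 26 | 41.2% | 51.0% (+9.8) | 46.4% (+5.2) |
| Cut-off, no floor, r = 0.58, 14 vs 26 | 61.5% | 80.1% (+18.6) | 73.1% (+11.6) |
| Reliable change of 15, all ≥ 33, r = 0.5, 14 vs 26 | 71.8% | 73.2% (+1.4) | 71.1% (−0.7) |

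Two further runs on inputs like those of A gave gains of about 7 to 13 and 9 to 13 points on the cut-off event. The second gave about 9 to 13 for a three-arm test as well. For reliable change it gave about 2 to 11 points, depending on threshold and variance split.

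**Level under no effect (cut-off event).** Plain log-rank 4.5 to 6.3% over all runs, adjusted log-rank 4.7 to 5.8%, stratified log-rank 4.8 to 5.4%. Baseline-adjusted Cox gave about 6 to 7% and a discrete-time logistic model 5.5 to 7.2%, both slightly liberal at this size.

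**Chance imbalance.** The standard error of the difference in baseline means is 12 × √(2/43) = 2.6 points. With no treatment effect, each point moves the log-rank Z by about 0.2, so an imbalance of one standard error moves it by about 0.2 × 2.6 = 0.5. Among simulated trials with an imbalance of at least 2.6 points, the plain test rejected in 8 to 11%.

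**The case against.** The strongest reply is that nothing here is an error. The log-rank test is a standard, valid choice, and randomization protects its level. Sections 2.5, 2.6.1.1 and 2.6.1.2 put baseline into comparisons of scores and never promise it for a time-to-event comparison. Covariates for a secondary survival analysis can also be left to a fuller document.

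Most of this stands. A reader might infer that the efficiency test is biased or has an inflated error rate; it is not and does not. The 8 to 11% applies only to trials selected for imbalance, and over all randomizations the test rejects at about 5%. A reader might also infer that the plan contradicts itself; it does not, because the adjustment in section 2.5 concerns CAPS-5 means after treatment.

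The argument from missing detail does not stand. Section 2.6.2 names the test, and a log-rank test ordinarily carries no covariate. Pointing to a better version of a stated method is not a complaint about omission.

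Three further limits are fair. The power figures are for a pairwise comparison, whereas the article specifies three conditions; the gain persists with three arms, but the absolute powers are not those of the planned test. In simulation A, adjusted power is still only 44 to 72%. And the article claims no power for aim 2.

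**Conclusion.** This is a cheap improvement to a valid but inefficient test, and it is worth making. For the cut-off event, adjusting for T0 PCL-5 adds roughly 7 to 15 points of power to a pairwise comparison at a correlation of about 0.5. Over correlations of 0.35 to 0.58 and the different methods the range is about 4 to 19. The gain was positive in every cut-off setting tried. Adjustment also makes the result less dependent on which arm happened to start nearer to 33.

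The size rests on inputs that the article does not give for PCL-5: mean, SD, rate of decline and efficiency effect. The correlation is borrowed from CAPS-5. No single figure for the loss should therefore be quoted as the plan's own.

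It would also be too strong to say that both events suffer alike. Reliable change is already measured from baseline, and the gain there ran from about 0 to 11 points, too unstable to support a firm claim.

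**What to change.** In section 2.6.2, pre-specify a covariate-adjusted log-rank test with continuous T0 PCL-5 as the deciding test for the cut-off event, for both the three-arm and the pairwise comparisons. A log-rank test stratified by baseline PCL-5 is a simpler alternative with a smaller gain. Applying either to reliable change is optional.

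Report a hazard ratio from a model with condition and T0 PCL-5 as a supporting estimate only. State that it is conditional on baseline, assumes proportional hazards and is slightly liberal at this sample size, so that the adjusted log-rank test prevails if the two disagree. Keep the unadjusted Kaplan-Meier curves as the display.

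The cost is a sentence or two of wording and a few lines of R, with no new data, visits or patients. The adjusted log-rank test adds no proportional-hazards assumption. The change should be fixed before outcome data are examined by arm, since a covariate added later would look data-driven.
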